#### Exclusion criteria

2.4.2

1.SAH secondary to nonaneurysmal entities such as hemorrhagic diatheses, trauma, tumor, or arteriovenous malformation, cavernous malformation;2.Early death due to rebleeding or other complications before surgery;3.Patients of extreme clinical severity, such as those with no spontaneous breathing, bilateral dilated pupils, or Hunt–Hess grade 5;4.Prior hydrocephalus or ventriculoperitoneal shunt, endoscopic third ventriculostomy, or FLT;5.Aneurysm beyond the access of surgical FLT including the distal anterior/middle cerebral aneurysms;6.DSA-negative SAH;7.Coagulopathy, or other known definite contraindication to operation;8.Patients complicated with vital organ dysfunction;9.Patient with poor compliance;10.Pregnant;11.Prior dementia or modified Rankin score (mRS) ≥3.

### Intervention

2.5

Patients allocated in the control group will undergo standard microsurgical aneurysm clipping via pterion approach within 3 days after stroke onset. Sharp dissection of sylvian cistern, and then carotid, chiasmatic cisterns will be made to decrease intracranial pressure and expose the aneurysm according to the preoperative angiography. The Liliequist membrane will also be opened. The neck of aneurysm is seen clearly and clipped correctly avoiding the near perforating artery occlusion and parental artery narrowing under microscope of high resolution. The subarachnoid clot around the basal cistern will be meticulously cleared away. We do not routinely perform ventriculostomy that is reserved for patients with decreased consciousness and acute hydrocephalus.

Patients in the interventional group will undergo an additional fenestration of laminal terminalis after the same aneurysm clipping procedure. FLT will be performed in the following steps: a self-retaining retractor adjusted parallel to the anterior communicating artery to completely expose the lamina terminalis that is a bluish, bulging membrane behind the optic chiasm; an incision about 5 mm in length made strictly in the midline of the lamina terminalis to avoid injury to the adjacent neurovascular structures; the opened rim briefly coagulated to avoid subsequent reclosure as a result of adhesions. Postoperatively, standard medical treatment will be used in accordance with the recommendation of the professional guideline.

The trial will be terminated in advance if apparent benefit or higher rate of severe AE in one of the 2 interventions is revealed at a high significance level that is defined as differences of more than 3 standard deviations. To improve the adherence of protocol intervention, surgeons are not allowed to change the interventional strategy once the randomized grouping is determined. In addition, the video record of the entire surgical process will be checked at random to monitor the consistency of intervention. External CSF drainage is prohibited during the operation in the trial.

### Outcomes

2.6

#### Primary outcome

2.6.1

The primary outcome of this trial is the incidence of shunt-dependent hydrocephalus confirmed by both clinical symptoms and CT scan at 1 year after operation. Clinical manifestation includes a progressive decline in neurological function (deterioration of mental status, urinary incontinence, gait disturbance, and memory impairment). The radiographic diagnosis of hydrocephalus is made on the basis of the ventriculomegaly with the following observations: enlarged frontal and temporal horns, enlargement of the third ventricle, a narrowed pattern of cortical sulci, and the presence of periventricular oozing. Ventricular size is determined by the cerebral ventricular index (the greatest width between the frontal horns at the level of the Monro foramen divided by the transverse inner distance of the cranium at the same level).^[26]^ Radiologically, hydrocephalus is diagnosed when the ventricular size exceeds the 95th percentile after adjusting for patient age. Whether or not shunt is placed depends on the following criteria: ventricular enlargement on radiological imaging stated above, the progressive neurological dysfunction, and the consequent improvement after lumbar drainage.^[31]^

#### Secondary outcomes

2.6.2

The major secondary outcomes are short-term and long-term neurological outcomes at 3 months and 1 year, respectively. The unfavorable outcomes indicate death and dependency which are defined as the modified Rankin Scale (mRS) score ≥3. Others will include the incidence of cerebral vasospasm and delayed cerebral ischemia within 1 month, the systematic complications, and days of hospitalization.

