**Methods/Design::**

A total of 288 patients who meet the inclusion criteria will be randomized into single aneurysm clipping or aneurysm clipping plus FLT in the Department of Neurosurgery, West China Hospital. Follow-up was performed 1, 3, 6, and 12 months after aneurysm clipping. The primary outcome is the incidence of SDH and the secondary outcomes include cerebral vasospasm, functional outcome evaluated by the modified Rankin Scale and Extended Glasgow Outcome Scale, and mortality.

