#### Sample size

2.6.3

The rate of SDH after anterior circulation aneurysm clipping was reported to range from 9.8% to 36% with an average rate of about 20% ,^[3,9,21]^ while the incidence of SDH was less than 5% in patients undergoing fenestration during aneurysm repair.^[8]^ We hypothesize that FLT can reduce the incidence of SDH from 20% to 5%. When statistical power is chosen to be 80% and a significant level to be 0.05 with a consideration of 10% loss to follow-up, a total of 288 patients are yielded with 144 patients in each arm.

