### Statistical analysis

2.7

The “intention to treat” analysis method will be adopted in this study. A simple comparison for rates of SDH, mortality, and cerebral vasospasm will be made by *χ*^2^ test or Fisher exact test. The functional outcomes will be analyzed by Mann–Whitney *U* test. The log-rank method will be used with regard to the analysis of time-to-event type of outcomes. Preset subgroup (including age, location of aneurysm, WFNS grades, Fisher grade, time to randomization, time to operation) analysis will be performed. We will use logistic regression model to adjust the effect of multiple variables.

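### The major secondary outcome is described only by the cut mRS ≥3 but assigned an unadjusted rank test, so full-scale and dichotomised analyses are both open; name one adjusted full-scale analysis as the main one

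*Protocol article*

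**What the plan says.** Section 2.6.2 of the protocol article ranks the functional endpoints first among the secondary outcomes: "The major secondary outcomes are short-term and long-term neurological outcomes at 3 months and 1 year, respectively". The only description of how they are scored follows: "The unfavorable outcomes indicate death and dependency which are defined as the modified Rankin Scale (mRS) score ≥3".

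Section 2.7 allots tests by type of outcome. The chi-square or Fisher test has a closed list: "A simple comparison for rates of SDH, mortality, and cerebral vasospasm will be made by" one or other of these tests. The proportion with mRS ≥3 is not on it. Instead, "The functional outcomes will be analyzed by Mann–Whitney" U. The same section adds "We will use logistic regression model to adjust the effect of multiple variables", without saying for which outcome.

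The abstract describes "functional outcome evaluated by the modified Rankin Scale and Extended Glasgow Outcome Scale, and mortality", with no cut-point. The Figure 1 legend also abbreviates both scales. Section 2.6.2 names only the mRS.

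Section 2.3.2 lists the minimization factors: age, Fisher grade, admission GCS and acute hydrocephalus.

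**The concern.** Section 2.6.2 suggests a comparison of two proportions, while 2.7 suggests a comparison of distributions over the whole scale. Nothing in the article says which form of the mRS enters the test, so two different analyses of the same data can each be presented as the planned one. The unassigned logistic regression widens this: applied to function, an ordinary logistic model would need the dichotomy, while the unadjusted test could use the full scale. Two time points and a second scale add further versions, and none is named as the main one.

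Two things are at stake. One is the false-positive risk for the leading secondary claim if the more favourable form may be reported. The other is efficiency: the one test named for function makes no use of the baseline factors that the trial considered important enough to balance on.

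**Working it through.** **Inputs.** The article gives no mRS distribution and no design figure for function. Its only computed figure, 288 patients, was set for the primary outcome and is used here only for the number evaluable: 144 per arm less 10% loss = 144 × 0.9 = 129.6, taken as 130. (The 288 does not follow from the stated inputs of 20% versus 5%, 80% power and 0.05. Two-sided, [1.96·√(2·0.125·0.875) + 0.842·√(0.20·0.80 + 0.05·0.95)]² / 0.15² gives 76 per arm, 85 after loss, 170 in all, or 196 with continuity correction. That is a separate matter and does not bear on this point.)

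**Step 1: is the named test valid on the dichotomy?** On a 0/1 variable the tie-corrected Mann–Whitney z equals the uncorrected chi-square z times √((N−1)/N). For 65/130 versus 50/130:
- difference = 15/130 = 0.1154; pooled proportion = 115/260 = 0.4423
- standard error = √(0.4423 × 0.5577 × 2/130) = 0.0616; z = 1.873; p = 0.0611
- Mann–Whitney z = 1.873 × √(259/260) = 1.869; p = 0.0616

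For 60/130 versus 45/130 the p-values are 0.0580 and 0.0585. On the dichotomy the two are practically one test, so the named test is valid for either form of the mRS.

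**Step 2: do the full-scale and dichotomised analyses differ?** Simulation, 40,000 trials per row, 130 per arm. Full scale: z = (W − n(N+1)/2)/√V, where W is the midrank sum and V = (n²/12)·[(N+1) − Σ(t³−t)/(N(N−1))]. Dichotomy: pooled two-proportion z on mRS ≥3. Both are two-sided at 1.96.

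No treatment effect, assumed percentages for mRS 0 to 6:

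| Assumed distribution | mRS ≥3 | Rank test rejects | Dichotomy rejects | Either rejects | Disagree |
|---|---|---|---|---|---|
| 10/20/20/15/15/5/15 | 50% | 5.1% | 5.5% | 7.6% | 4.7% |
| 15/25/20/12/10/5/13 | 40% | 5.1% | 5.0% | 7.5% | 4.9% |
| 5/15/15/20/20/10/15 | 65% | 4.9% | 5.1% | 7.6% | 5.3% |

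The two z statistics correlate at 0.84 to 0.88, so they are closely related but not interchangeable.

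Common odds ratio applied to the first distribution:

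| Odds ratio | Power, rank test | Power, dichotomy | Disagree |
|---|---|---|---|
| 1.5 | 46% | 38% | 17% |
| 1.7 | 68% | 57% | 18% |
| 2.0 | 88% | 79% | 13% |

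A further control distribution (10/18/15/15/12/8/22, 8,000 trials) gives 7.6% for either test under no effect. At an odds ratio of 1.8 it gives power of 77% versus 67%, with 15% disagreement.

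**Step 3: what does adjustment offer?** With one assumed prognostic covariate, power rose from about 60% for the unadjusted rank test to about 72% for an adjusted proportional-odds model. A check on the last distribution above (600 trials each, one standard normal covariate, conditional odds ratio 1.8) gave 66% to 75%, 64% to 75% and 55% to 72% for covariate log odds ratios of 0.8, 1.0 and 1.2 per standard deviation. The documents do not say how strongly the minimization factors predict function, so this shows direction and order of size only.

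**The case against.** The strongest reply is that nothing here is wrong. Section 2.6.2 says what an unfavourable outcome is; it does not say that the mRS will be analysed only as a dichotomy. The abstract gives both scales without a cut-point, and 2.7 gives functional outcomes a single rank test. Read together, these suggest an ordinal analysis with mRS ≥3 as a clinical label. The 7.5% arises only if someone also runs a test of the dichotomy that 2.7 does not assign and then picks the better result.

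Much of this stands, and it rules out several stronger readings that a reader might infer:
- **That the plan contradicts itself.** It does not; the ordinal reading is available.
- **That the defined outcome has no matching test.** Step 1 shows the named test serves either form.
- **That the lack of an effect estimate is a defect.** Effect measures and intervals are commonly left to the analysis plan, which is not shown.
- **That the plan makes no provision for adjustment.** It plans a logistic regression, although it names no outcome for it.

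The reply does not remove the ambiguity. The only description of the outcome in 2.6.2 is a cut-point, no sentence says which form is tested, and the logistic regression is a natural route back to the dichotomy. The absence of the Extended Glasgow scale from 2.6.2 may be condensation for the journal, but it leaves the scale without a role.

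**Conclusion.** The point holds as an ambiguity with an inexpensive improvement, in a secondary outcome. The named test is valid, but the form of the outcome is not settled, and the test leaves aside the factors used in minimization. If either form may be reported, the false-positive risk is about 7.5% per time point instead of 5%; a second time point and a second scale would widen the choice further, by an amount not calculated here. Under common odds ratios of 1.5 to 2.0 the two forms disagree on significance in about 13% to 18% of trials, and the full scale has roughly 8 to 11 points more power. These figures assume 130 evaluable per arm, the mRS distributions shown and, for power, proportional odds. The 7.5% varied little across the distributions tried; the gain from adjustment depends on an assumed covariate strength. The comparison of shunt-dependent hydrocephalus is unaffected.

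**What to change.** In 2.6.2 and 2.7, before outcome data are seen, state that:
- the main functional analysis is the full mRS (0–6, death = 6) at 1 year, by a proportional-odds model adjusted for age, Fisher grade, admission GCS and acute hydrocephalus;
- the 3-month mRS is analysed the same way;
- the proportion with mRS ≥3 and the Extended Glasgow Outcome Scale are supportive.

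The cost is a few sentences. The minimization factors are already recorded, so sample size, visits and data collection do not change. The downside is that the proportional-odds assumption needs a check. Naming the full-scale Mann–Whitney test as the main analysis would also settle the ambiguity, but it would forgo the gain from adjustment.

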#### Sample size

2.6.3

The rate of SDH after anterior circulation aneurysm clipping was reported to range from 9.8% to 36% with an average rate of about 20% ,^[3,9,21]^ while the incidence of SDH was less than 5% in patients undergoing fenestration during aneurysm repair.^[8]^ We hypothesize that FLT can reduce the incidence of SDH from 20% to 5%. When statistical power is chosen to be 80% and a significant level to be 0.05 with a consideration of 10% loss to follow-up, a total of 288 patients are yielded with 144 patients in each arm.

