Traditionally, ventriculoperitoneal shunt is the treatment of choice after SDH. However, CSF shunts have high malfunction rates with reported 43% and 85% of shunts failure at 1 and 10 years after the first placement, respectively.^[22]^ Moreover, the procedure of shunt placement or revision has the risk of intracerebral hemorrhage,^[23]^ CSF leakage, infection, and bowel perforation or pneumothorax, with mortality up to 7% to 9% in selective populations.^[22,24,25]^ Specifically, although SDH after aSAH was considered less frequently to suffer shunt failure compared with other forms of hydrocephalus, 30% patients required a subsequent revision which contributed to multiple revisions.^[15]^

Fenestration of lamina terminalis (FLT) is a useful procedure during ruptured aneurysm surgical clipping to allow brain relaxation under increased intracranial pressure by offering free CSF flow from the third ventricle to the basal cistern. In addition, FLT has been performed to prevent the occurrence of SDH through facilitating CSF circulation, clearance of blood in basal cisterns, and improving CSF dynamics.^[8]^ Tomasello et al^[26]^ first assessed the effect of FLT in preventing SDH in 1999. Of the 52 patients included, only 2 (4.2%) patients developed SDH with a follow-up of 12 to 60 months. Since then, more than 400 patients were treated combining FLT, clot evacuation from the basal cisterns, and opening of the Liliequist membrane with the incidence of SDH less than 4%. Komotar et al^[27]^ in 2002 further confirmed the usefulness of FLT in a large population (582 cases) as they showed a decreased incidence of SDH in more than 80% patients with aSAH. Moreover, it was demonstrated that FLT was not also associated with reduced SDH, but also with decreased vasospasm and better outcome.^[28]^ Hence, FLT was recommended as a routine practice in patients with severe aSAH.^[27]^

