However, the therapeutic role of FLT is questioned by recent studies. Komotar et al^[29]^ failed to observe decreased SDH as fenestrated patients had a shunt rate of 25% compared with 20% in unfenestrated patients. The negative results were supported by Chohan et al^[30]^ who intraventricularly injected a contrast agent to evaluate the functional patency of the fenestrated lamina terminalis with CT imaging, finding that contrast agent followed the normal ventricular pathway into fourth ventricle rather than in the basal cisterns. To define the controversial role of FLT, a systematic review including 11 studies involving 1973 patients was performed where no significant association between FLT and a reduced incidence of SDH was revealed with an overall incidence of 10%, 14% in the fenestrated and nonfenestrated cohort, respectively.^[13]^ However, the baseline data between the 2 cohorts were inconsistent, especially with more patients in poor clinical condition in the former. Actually, high grade SAH is a risk factor of the occurrence of SDH,^[17,18]^ so this difference reinforced the efficacy of FLT. Therefore, a well-designed randomized controlled trial is widely called on to definitively determine the efficacy of this technique.

To the best of our knowledge, only a single randomized controlled study was performed to address such debate.^[7]^ This clinical trial included 50 patients with ruptured anterior communicating aneurysm, suggested no significant difference between fenestrated and nonfenestrated group (24% vs 16%). However, more than 90% patients with low grade SAH and about 60% with Fisher grade I/II were included which underpowered to detect the difference as patients with low grade of H-H Grade or Fisher Grade are quite less likely to develop SDH. In addition, this study was obviously limited by the quite small sample size.

We designed this study to provide more robust evidence of the efficacy of FLT during surgical aneurysm clipping on the prevention of SDH with a large sample size and strict inclusion and exclusion criteria.

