#### Randomization

2.3.2

Patients will be allocated to either single aneurysm clipping group or aneurysm clipping plus FLT group by the minimization method that is performed by a minimization software. The stratification factors for minimization include age, Fisher grade, admission GCS, and acute hydrocephalus. Once a patient is qualified, the baseline information including demographics, medical history, time from SAH onset, Hunt–Hess grade, Fisher grade, and physical examination of the patient will be sent to a special researcher who is in charge of patients randomization.

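### The 20% to 5% effect used for sizing is not shown to apply to the randomized contrast, which is FLT added to clipping with clot clearance and Liliequist opening, and the stated 80% power is not the power that 288 patients give

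*Protocol article*

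**What the plan says.** Sample size (2.6.3) sets the effect: "We hypothesize that FLT can reduce the incidence of SDH from 20% to 5" per cent. The control figure is the rate after anterior circulation clipping, which "was reported to range from 9.8% to 36% with an average rate of about 20" per cent. The other figure is given in these words: "while the incidence of SDH was less than 5% in patients undergoing fenestration during aneurysm repair". With 80% power, a 0.05 significance level and 10% loss to follow-up, the section arrives at 288 patients, 144 per arm.

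Intervention (2.5) describes the control operation. Besides clipping, it says "The Liliequist membrane will also be opened" and "The subarachnoid clot around the basal cistern will be meticulously cleared away". The FLT arm has the same procedure with fenestration added.

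The Background reports that "more than 400 patients were treated combining FLT, clot evacuation from the basal cisterns, and opening of the Liliequist membrane", with SDH below 4%. It also reports a 52-patient FLT series with 2 cases of SDH.

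The Abstract and Randomization (2.3.2) name the comparator without those two steps: "Patients will be allocated to either single aneurysm clipping group or aneurysm clipping plus FLT group by the minimization method".

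**The concern.** A sizing assumption should describe the difference between the two arms as they will be treated. Here it is formed by subtracting a rate in fenestrated patients from an average rate after clipping, each from a different source. Nothing in the Sample size section says what else was done in either group.

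That matters because the control arm receives two of the three steps in the below-4% experience. If those steps prevent some SDH, the control rate in this trial could lie below the general clipping average, and the arms would be closer together than planned. The trial would still answer a sensible question, namely what FLT adds to clot clearance and Liliequist opening, but with less power than a reader of the section would expect. The comparator label in the Abstract and under Randomization would then let a null result be read as a verdict on FLT against plain clipping. The article says that the trial will settle the debate on FLT, so both the contrast and the power should be stated correctly.

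**Working it through.** **Inputs.** From Sample size: control 20%, FLT 5%, 80% power, alpha 0.05, 10% loss, 144 per arm. Sidedness is not stated; two-sided is assumed. The primary test is chi-square or Fisher exact (Statistical analysis, 2.7). Evaluable per arm: 144 × 0.90 = 129.6, taken as 130.

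**Step 1: the plan's own figure.** The pooled two-proportion formula is

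n = [1.96·√(2p̄(1−p̄)) + 0.842·√(p₁(1−p₁) + p₂(1−p₂))]² / (p₁−p₂)²

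With p₁ = 0.20, p₂ = 0.05 and p̄ = 0.125: (0.917 + 0.383)² / 0.0225 = 75.1, so 76 per arm. Dividing by 0.90 gives 85 per arm, or 170 in total. With a continuity correction it is 88, then 98 per arm, or 196 in total. One-sided, unpooled and arcsine versions give smaller totals than their two-sided pooled counterparts. At 90% power the two-sided totals are 226, or 254 with continuity correction. No version tried reproduces 288 at 80% power.

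**Step 2: the power that 288 gives at the stated rates.**

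z = [√n·(p₁−p₂) − 1.96·√(2p̄(1−p̄))] / √(p₁(1−p₁) + p₂(1−p₂))

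With n = 130: (1.710 − 0.917) / 0.456 = 1.74, so power is about 96%. Fisher's exact test with 129 per arm gives 95%.

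**Step 3: where the design has 80% power.** For 20% vs 8%: (1.368 − 0.962) / 0.483 = 0.84, so 80%. Holding the FLT arm at 5%, 80% is reached with a control rate of about 15.5%.

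**Step 4: other rates** (130 per arm, same formula).

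| Control | FLT | Power | Origin of the rates |
|---|---|---|---|
| 20% | 5% | 96% | Sample size section |
| 25% | 10% | 89% | assumption |
| 20% | 8% | 80% | assumption (detectable limit) |
| 15% | 5% | 77% | assumption |
| 20% | 10% | 62% | assumption |
| 14% | 10% | 17% | systematic review cited in the Background |

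**Step 5: the article's own comparative data.** Three comparisons in the Background give rates for both groups. The systematic review reports SDH "with an overall incidence of 10%, 14% in the fenestrated and nonfenestrated cohort, respectively". A later series has 25% with fenestration and 20% without, and the one previous randomized trial has 24% and 16%. The differences are 4 points in favour of FLT, 5 points against and 8 points against. None is near 15 points in favour.

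**The case against.** The strongest reply is that the FLT arm receives all three steps, so 5% may suit that arm whatever procedure it came from. That stands, and it is why the control rate, not the 5%, is the weak input.

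A reader might go further and infer that the 5% is the three-step rate, so that the sizing compares a full bundle with ordinary clipping. The article does not support this. The Sample size section takes the figure from a reference described only as patients undergoing fenestration. The sentence on the three-step experience carries no citation, and the 52-patient series is presented as a study of FLT. Nothing shows that the series behind the 20% omitted clot clearance or Liliequist opening; the article calls its control operation standard. It gives no separate effect of either step on SDH.

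A reader might also infer that the trial is underpowered. That is not shown either. The surplus over about 170 patients absorbs a fall in the control rate to about 15.5%. Enrolment is limited to Fisher 3–4 and Hunt–Hess 3–4, the article names high grade as a risk factor, and its reported range reaches 36%, so the control rate could exceed 20%.

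The authors also discount the comparative data. They say that the review's cohorts were unbalanced, with more patients in poor condition in the fenestrated group, and that the small trial enrolled mostly low-grade patients and was too small. The Background further cites a 582-case study as favourable, though its figure of more than 80% is worded too unclearly to use as an effect size. These points make the FLT effect uncertain; they do not establish a 15-point one.

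Finally, the main objective in Study design (2.1) compares clipping plus FLT or not, and Intervention describes the contrast correctly. The labelling problem is confined to the Abstract and Randomization.

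**Conclusion.** The point holds in a limited form. The article does not show that 20% vs 5% applies to FLT added to clipping with basal clot clearance and Liliequist opening, because the two rates come from different sources and the control rate is not justified for this control operation. Separately, the power statement is wrong for its own inputs: about 96% rather than 80% at 20% vs 5%, or about 170 patients rather than 288.

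What 288 buys is 80% power at about 20% vs 8% or 15.5% vs 5%. Power falls to 62% at 20% vs 10% and to 17% at 14% vs 10%. These figures assume a two-sided 0.05 test and 130 evaluable per arm. All rate pairs except 20% vs 5% and 14% vs 10% are assumptions chosen to show the range. Whether power is in fact inadequate depends on the control rate in this high-grade population and on FLT's true increment, neither of which the article establishes.

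**What to change.** Keep 288 patients and leave the operation as it is.

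1. In Sample size, replace the statement of 80% power at 20% vs 5% with what 288 gives: about 96% at those rates, with 130 evaluable per arm and a two-sided 0.05 test. State the smallest difference detectable with 80% power, about 20% vs 8%.
2. In the same section, show power for control rates below and above 20% and for smaller FLT effects, for example 15% vs 5% (77%), 20% vs 10% (62%), 14% vs 10% (17%) and 25% vs 10% (89%). Mark which rates are assumptions.
3. In the Abstract and under Randomization, describe the comparator as clipping with basal clot clearance and Liliequist opening, so that the conclusion is limited to FLT's added effect.

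Do not write that the 5% comes from the three-step procedure; the article does not show it. The cost is a few sentences, with no extra patients or procedures. The downside is that power will look less favourable under smaller effects.

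### The stated inputs (20% vs 5%, 80% power, alpha 0.05, 10% loss) give 170 to 196 patients, not 288; at 288 the power for that hypothesis is about 96%

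*Protocol article*

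**What the plan says.** The whole derivation stands in the Sample size section (2.6.3) of the protocol article.

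- Effect: "We hypothesize that FLT can reduce the incidence of SDH from 20% to 5" percent. The lower rate is supported by the remark that "the incidence of SDH was less than 5% in patients undergoing fenestration during aneurysm repair".
- Power: "When statistical power is chosen to be 80" percent.
- Significance level: "a significant level to be 0.05", with no statement of one- or two-sided.
- Attrition: "with a consideration of 10% loss to follow-up".
- Result: "a total of 288 patients are yielded with 144 patients in each arm".

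The endpoint is binary (shunt-dependent hydrocephalus, SDH, at 1 year; section 2.6.1). Section 2.7 compares SDH rates by chi-square or Fisher exact test, so a two-proportion calculation is the right one. The article gives no formula, no continuity correction and no other reason for a larger number.

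**The concern.** The section gives the effect, power, significance level, attrition and allocation, and presents 288 as their result. A reader can therefore redo the sum, and it does not come out. This is not a detail lost in condensing a longer protocol, because the inputs and the output are both printed and disagree.

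At stake is how the result will be read. The article says the trial is meant to settle a long-standing debate, so a null result must be interpretable. As written, it would be set against a 15-point difference at 80% power. At the stated size the trial has about 96% power for that difference, and about 80% power for a difference nearer 12 points. A reader also cannot see why the stated hypothesis needs 92 to 118 more patients than its own inputs imply (288 − 196 and 288 − 170).

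**Working it through.** **Inputs**, all from section 2.6.3: p1 = 0.20, p2 = 0.05, d = p1 − p2 = 0.15, power 80% (z = 0.8416), alpha 0.05 (two-sided z = 1.9600; one-sided z = 1.6449), 10% loss, 1:1 allocation. Two-sided testing is assumed first because sidedness is not stated.

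**Step 1. Try to reproduce 288.** Pooled-variance formula, with p̄ = (p1 + p2)/2 = 0.125:

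n = [z_alpha × √(2p̄(1 − p̄)) + z_power × √(p1(1 − p1) + p2(1 − p2))]² / d²

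- First term: 1.9600 × √0.21875 = 0.9167
- Second term: 0.8416 × √0.2075 = 0.3834
- n = (1.3001)² / 0.0225 = 75.1, so 76 per arm
- After loss: 76 / 0.9 = 84.4, so 85 per arm, **170 in total**

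Continuity correction, n' = (n/4) × [1 + √(1 + 4/(n × d))]²:

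- 4/(75.1 × 0.15) = 0.355; n' = 18.78 × (2.164)² = 87.9, so 88 per arm
- After loss: 88 / 0.9 = 97.8, so 98 per arm, **196 in total**

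The stated 288 is not reproduced. It exceeds these totals by 69% (288/170) and 47% (288/196).

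**Step 2. Try other conventions with the same stated inputs.**

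| Variant | Total after loss |
|---|---|
| Two-sided, pooled | 170 |
| Two-sided, continuity correction | 196 |
| Two-sided, unpooled variance | 164 |
| Two-sided, arcsine | 156 |
| One-sided, pooled | 134 |
| One-sided, continuity correction | 160 |

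Inflating by × 1.1 instead of / 0.9 changes the two-sided pooled and corrected totals only to 168 and 194. Fisher exact power, by enumeration, is already 82% at 85 per arm, which is 95 per arm after loss (85 / 0.9 = 94.4), or 190 in total. No variant exceeds 196. To reach 144 per arm from 76 or 88, the loss would have to be 47% (1 − 76/144) or 39% (1 − 88/144), not 10%.

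**Step 3. Power at the stated size.** Evaluable per arm: 144 × 0.9 = 129.6, about 130.

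z_power = [d × √n − z_alpha × √(2p̄(1 − p̄))] / √(p1(1 − p1) + p2(1 − p2))

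- 20% vs 5%: (0.15 × 11.402 − 0.9167) / 0.4555 = 1.742, power **95.9%** (Fisher exact 95.2% at 129 per arm)
- 20% vs 8%: (0.12 × 11.402 − 0.9618) / 0.4833 = 0.841, power **80.0%** (Fisher exact 75.7% at 129 per arm)

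**Step 4. Can the misreported input be identified?** These sets, all with 10% loss, were compared with 288. The test is two-sided and pooled unless marked.

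| Inputs | Total |
|---|---|
| 20% vs 8%, 80% power, alpha 0.05 | 292 (328 with continuity correction) |
| 14% vs 4%, 80% power, alpha 0.05 | 286 |
| 17% vs 6%, 80% power, alpha 0.05 | 292 |
| 20% vs 5%, 80% power, alpha 0.005 | 286 |
| 20% vs 5%, 90% power, alpha 0.05 | 226 (254 with continuity correction) |
| 20% vs 5%, 95% power, alpha 0.05 | 276 (306 with continuity correction) |

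Several different sets land within a few patients of 288, so the total does not reveal which input differs from the one used.

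**The case against.** The strongest reply is that the error does no harm to the trial's own aim. The sample is larger than the stated hypothesis needs, power for 20% vs 5% is about 96%, and the planned test is untouched. A null result would say more about a 15-point effect than the text claims. That stands, and it limits the weight of the point. It does not make the printed derivation correct.

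A second reply is that sidedness and formula are details an article may leave to the full protocol. That is fair as far as it goes, but no choice of either recovers 288 from the printed inputs.

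Three stronger readings are tempting, and the document does not support them.

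- *That 288 was calculated for 20% vs 8%.* The 8% is a back-calculation and is nowhere a design assumption. Rounded up in the usual way it gives 292, and other inputs fit as well. The effect, the power, the significance level, an unstated inflation or the total itself could be the misreported item.
- *That power is really about 17%, because the Background reports a systematic review* "with an overall incidence of 10%, 14% in the fenestrated and nonfenestrated cohort, respectively". The same section says those cohorts differed at baseline, with more poor-condition patients among the fenestrated. This trial takes only Fisher grade 3–4 and Hunt–Hess grade 3–4. Those rates are not its planning values and have no bearing on the arithmetic.
- *That the 5% rate is invalid because the Background describes patients* "treated combining FLT, clot evacuation from the basal cisterns, and opening of the Liliequist membrane with the incidence of SDH less than 4" *percent, and here both arms receive the last two steps.* Section 2.6.3 cites a different reference for its rate of under 5%, and nothing shown says the two are the same series. That is a separate question of design.

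**Conclusion.** The sample size statement is wrong as written: the printed inputs give 170 patients (196 with continuity correction), not 288. At 288, with about 130 evaluable per arm, power for the stated hypothesis is about 96% instead of 80%.

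The size of the mismatch rests on two-sided testing at 0.05, and one-sided testing widens it. The 96% also rests on 10% loss leaving about 130 evaluable per arm. The statement that 80% power corresponds to about 12 points holds only if the control rate is 20%. Section 2.6.3 itself reports a range of 9.8% to 36%. Under Fisher's exact test the power for 12 points is nearer 76%.

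A reader might infer that the trial is underpowered. It is not, for the hypothesis it states, because the error is on the large side. The defect is in the reporting and is cheap to correct.

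**What to change.** Keep 288. In section 2.6.3, state the formula, the sidedness and the inputs actually used, so that effect, power and sample size agree.

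- If the 20%-to-5% hypothesis stands, restate the power as about 96% at 130 evaluable per arm (two-sided 0.05). Add that, if the control rate is 20%, 80% power corresponds to a difference of about 12 points.
- If another effect, significance level or inflation was used, state it and give its source. An 8% rate should not be written in simply because it fits.

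The cost is one or two sentences. Enrolment, allocation and the planned test do not change.
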